### Outcomes

The primary outcome is symptomatic COVID-19, defined by the presence of at least one COVID-19-like symptom as listed in Participants section and confirmed by a positive RT-PCR result for SARS-CoV-2 infection from participants’ NP or nasal swabs.

Secondary outcomes are: (1) symptomatic SARS-CoV-2 infection associated with circulating variants (e.g., Delta, and Omicron); (2) duration of COVID-19 symptoms; (3) hospitalization for COVID-19 within 30 days from enrollment among patients with confirmed COVD-19; (4) need for ICU admission within 30 days from enrollment among patients with confirmed COVD-19; (5) need for invasive mechanical ventilation within 30 days from enrollment among patients with confirmed COVD-19; (6) death from COVID-19 within 90 days from enrollment among patients with confirmed COVD-19; (7) health-related quality of life at 90 days from enrollment among patients with confirmed COVD-19, measured by the three-level version of the EuroQol five-dimensional descriptive system (range, -0.17 [worst] to 1.0 [best]; minimal important difference, 0.03) [7, 8]; (8) persistent COVID-19 symptoms at 180 days from enrollment among patients with confirmed COVD-19; (9) symptomatic SARS-CoV-2 reinfection within 365 days from enrollment among patients with confirmed COVD-19, defined as recurrence of COVID-19-like symptoms confirmed by a positive RT-PCR or antigen test for SARS-CoV-2 more than 90 days after primary infection.

Safety data including adverse events and serious adverse events will be assessed upon inclusion of cases and controls and over the 12-month follow-up for cases, under the standard of care procedures for the city of Toledo’s surveillance program per Brazilian regulatory authority’s requirements.

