**Fig 2 pone.0276384.g002:**
[figure not shown]
Schedule of enrollment and assessment. N/A. Not appliable; RT-PCR, reverse transcriptase polymerase chain reaction.

Baseline assessment is performed by trained researchers at each participating site at the time an eligible participant with symptoms of COVID-19-like illness seeks care through the public healthcare system. The vaccination status is assessed through structured interviews and adjudicated through review of city medical registry records reviews. Telephone follow-up is conducted via a single central telephone system located in the study coordinating centre (Hospital Moinhos de Vento). Therefore, all participants who are eligible for telephone follow-up (cases), regardless of the site of inclusion, are followed up by researchers trained in good clinical practices and in standardized telephone interview methods. The reference date for scheduling telephone interviews is the date of inclusion in the study. Interviews are considered lost if the participants’ telephone lines are disconnected or non-existent or after 10 attempts at different times on several days within a 5-day time window (5 days after the estimated interview date) for the 15-day interview, and 15-day time window (15 days after the estimated interview date) for the 1-, 3-,6-,9-, and 12-month interviews. Regardless of whether an interview is lost or not, contact is attempted at the subsequent scheduled interviews. This follow-up methodology has been used in previous observational studies [10, 11].

The data are collected using smartphone-, tablet- or computer-based electronic case report forms available on the *Otus* platform (https://site.otus-solutions.com.br/). Access to databases on this platform are granted only by the principal investigator to research team members through a personal, non-transferable username and password. An encrypted digital certificate is used to ensure security in data handling. Platform users (team members) have specific permissions related to their role in the study.

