#### Handling missing data

No data imputation will be performed for main exposure (vaccination status) and for the study outcome. Main analysis will consist of observed data, without imputation. For sensitivity analysis we will perform multiple imputation if missing data on core variables is > 5%, under the assumption that the missingness pattern is missing at random conditional on the observed data. Core variables are defined as the covariates to be used in the primary analysis: age, gender, Charlson comorbidity index [18], current smoking status, and body mass index (BMI) category.

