#### Secondary outcome analyses

The association between the exposition variables with symptomatic SARS-CoV-2 infection caused by circulating variants as well as the association between secondary exposition variables with symptomatic SARS-CoV-2 infection will be assessed using the same statistical model used for the primary outcome.

Crude and adjusted generalized linear models will be used to assess the impact of exposures on duration of COVID-19 symptoms, hospitalisation for COVID-19, need for ICU admission, need for invasive mechanical ventilation, death from COVID-19, health-related quality of life, persistent COVID-19 symptoms, symptomatic SARS-CoV-2 reinfection among participants with a positive RT-PCR result for SARS-CoV-2, and to test associations between length of time after receipt of the second or third dose of BNT162b2 and the risk of symptomatic SARS-CoV-2 infection, according to the probability distribution of each outcome. Quantitative outcomes will be expressed as mean difference. Categorical outcomes will be expressed as hazard ratio or relative risk as appropriate.

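### Duration of symptoms is assigned a plain mean difference, although it can be right-censored at 12 months, at loss to follow-up or at death

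*Protocol article*

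**What the plan says.** The second secondary outcome in the Outcomes section is "2) duration of COVID-19 symptoms". Unlike the outcomes listed after it, it has no time window. The Secondary outcome analyses section then says "Crude and adjusted generalized linear models will be used to assess the impact of exposures on duration of COVID-19 symptoms", with the other outcomes measured in cases, the model to be chosen "according to the probability distribution of each outcome".

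Two sentences assign the effect measures: "Quantitative outcomes will be expressed as mean difference" and "Categorical outcomes will be expressed as hazard ratio or relative risk as appropriate". Duration is a quantity. Of the other outcomes in that list, only health-related quality of life is clearly one too. The hazard ratio, the only time-to-event measure named, goes to categorical outcomes.

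Three other places bear on the point:
- **Outcomes** lists "persistent COVID-19 symptoms at 180 days from enrollment among patients with confirmed COVD-19" as a separate outcome, so some long illnesses are expected. It also lists death within 90 days.
- **Data collection** schedules calls to cases at 15 days and at 1, 3, 6, 9 and 12 months. It foresees lost interviews, and adds "Regardless of whether an interview is lost or not, contact is attempted at the subsequent scheduled interviews".
- **Handling missing data** says "No data imputation will be performed for main exposure (vaccination status) and for the study outcome" and bases the main analysis on observed data.

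**The concern.** Duration of symptoms is a time-to-event outcome. It is learned from calls that are two to three months apart after the first month, so for later recoveries the calls alone only bracket the day of resolution. For some cases it will never be observed: those still ill at the last call, those lost for good, and those who die.

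An ordinary generalized linear model for a mean needs one completed value per person. Choosing a gamma or similar distribution deals with skewness but not with censoring. The analyst is left with two options: omit the unresolved cases, or enter time to last contact as if the illness had ended then. Both weaken the contribution of the longest illnesses. Entering a fatal case at the day of death makes the worst outcome look like a quick recovery, so higher mortality in one group would read as shorter illness in that group.

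At stake is the credibility of one secondary estimate, and the risk that the handling of unresolved cases is chosen after the data are seen.

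**Working it through.** **1. Is there a figure in the plan to reproduce?** No. The article gives no expected duration, standard deviation, persistence rate, loss rate or death rate among cases. What follows is an illustration on assumptions.

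**2. When is a duration incomplete?** Setting the sections side by side gives three situations: symptoms continuing at the end of the 12-month follow-up, permanent loss before recovery, and death before recovery. Being symptomatic at 180 days is not one of them, because calls continue at 9 and 12 months. A single missed call is not one either, because contact is tried again at the next call.

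**3. Assumptions.** Short illness is lognormal with median 10 days and log-scale SD 0.6 in both groups. Its mean is A = 10 × exp(0.6²/2) = 11.97 days. A share p has long illness lasting 30 days plus an exponential time with mean m. The share p is 5–30% in unvaccinated cases and half that in vaccinated cases, and m is 150 or 300 days. All cases are followed to 365 days with no loss or death.

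**4. Formulas.** Let pU and pV be the long-illness shares, and let e = exp(−335/m) be the proportion of long illnesses unresolved at 365 days.
- True difference = (pU − pV) × (30 + m − A)
- Cut off at 365 days = (pU − pV) × (L − A), where L = 30 + m(1 − e)
- Unresolved dropped: the mean in each group is [(1 − p)A + pS] / [1 − p·e], where S = L − 365e; then take the difference

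**5. Numbers for 10% versus 5% long illness.**

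| | m = 150 | m = 300 |
|---|---|---|
| e | 0.107 | 0.327 |
| True difference | 0.05 × (180 − 11.97) = 8.4 days | 0.05 × (330 − 11.97) = 15.9 days |
| L | 163.9 | 231.8 |
| Cut off at 365 | 0.05 × (163.9 − 11.97) = 7.6 days | 0.05 × (231.8 − 11.97) = 11.0 days |
| S | 124.8 | 112.3 |
| Means after dropping | 23.5 and 17.7 | 22.75 and 17.27 |
| Difference after dropping | 5.8 days | 5.5 days |

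A simulation with 2,000,000 cases per group gives the same results to one decimal.

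**6. Range over all scenarios (simulation).** Cutting off at 365 days keeps about 69% (32.96 of 47.84 days) to 91% (22.72 of 25.10 days) of the true difference. Dropping unresolved cases keeps about 34% (2.70 of 7.93) to 71% (17.93 of 25.10). In every scenario the estimate moves towards no effect. Permanent loss before month 12 and deaths are not in these figures, and the documents give no rate from which to add them.

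**The case against.** The strongest reply is that the article states no rule for unresolved, lost or fatal cases, and that such detail commonly sits in a full protocol or analysis plan that is not shown. That stands as far as it goes: the missing rule is not the point. What remains is the model and effect measure that the article does state, which do not suit an outcome that can be censored. A later plan that followed this text would inherit the problem.

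Several stronger readings are tempting and are not supported:
- **That long durations are dropped or cut off under the plan.** Nothing in the article says so. This is what an ordinary mean model would force, not a stated procedure.
- **That anyone ill at 180 days is censored.** Calls continue to 12 months, so recovery after 180 days can still be observed.
- **That most of the effect is lost.** That needs a cut-off at 30 or 90 days, or removal of every persistent case. The article uses those days for other outcomes, not for symptom duration. Take assumed short illness of 12 versus 10 days, with 10% versus 7% persistent at an average of 270 days. The means are 0.9 × 12 + 0.1 × 270 = 37.8 and 0.93 × 10 + 0.07 × 270 = 28.2, a difference of 9.6 days. If each persistent case lasts 270 days, a cut at 365 days leaves all 9.6.
- **That censoring becomes informative because persistence differs by vaccination.** At a fixed 12-month horizon it does not; that difference is the effect being estimated.
- **That the no-imputation rule certainly covers duration.** It refers to the study outcome in the singular and may mean the primary outcome only.

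Two further replies hold. Persistent symptoms at 180 days are analysed separately without needing a completed duration, so the long-COVID question does not rest on this estimate alone. And secondary analyses are declared exploratory in the Overall principles section.

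**Conclusion.** The point holds in limited form. The article ties a duration with no time window to a mean difference from a generalized linear model, and that method cannot accommodate durations unresolved at month 12, at permanent loss or at death. The natural reading covers duration, although the mean-difference sentence does not name it.

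The bias runs towards no effect if vaccination shortens long illness. Its size in this study cannot be established from the documents. The retained shares of 69–91% and 34–71% rest wholly on assumed durations, on complete follow-up to 365 days, and on taking the unrestricted mean as the target. A declared mean up to day 365 would be a legitimate target in itself, but the article does not declare one, and lost and fatal cases would still need proper handling. The primary analysis is unaffected.

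**What to change.** For this outcome, replace the plain mean difference in the Secondary outcome analyses section with one of two analyses:
- **Time from symptom onset to resolution**, censored at the last completed interview, interval-censored between calls, with death as a competing event. Report cumulative incidence of resolution and an adjusted hazard ratio.
- **Adjusted difference in restricted mean symptom time** up to a pre-stated day within the 12-month follow-up, estimated by a method that accounts for censoring.

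State the time window in the Outcomes section, and say how unresolved, lost and fatal cases enter. Do this before the database is locked, so that the cut-off is not chosen from the data.

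The cost is a change of wording and of analysis code. No new contacts are needed: calls are already scheduled from the date of inclusion, and the exposure definitions already require the onset date. The article does not say whether a resolution date is recorded; symptom status at each call is enough for the interval-censored analysis. The downsides are that a hazard ratio is harder to read than days, and that a restricted mean describes duration only up to the chosen day.

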### Ethics and dissemination

The study complies with Brazilian National Health Council Resolution no. 466/12 [21]. The study protocol has been approved by the National Commission of Research Ethics (CONEP; CAAE, 50293121.9.0000.5330; opinion number, 4.911,499) and research ethics committee of all participant sites. All participants provide informed consent to participate prior to inclusion in the study. Participants younger than 18 years also provide written informed assent. For persons who lack the cognitive or physical conditions necessary to provide consent, consent to participation is obtained from family proxies.

Results from this study will be disseminated through peer-reviewed publications and conference presentations, addressing primary objective and secondary objectives. Authorship will be defined according to the International Committee of Medical Journal Editors (ICMJE) recommendations [22].

## Study status

The study design and protocol were finalised in October 2021. The first participant was included on November 3, 2021. At study start, approximately 2/3 of the target population was fully vaccinated. Two thousand and thirty-four participants were enrolled up to February 2, 2022. Currently, this study is recruiting participants in 3 referral COVID-19 sites in Toledo. We anticipate that the recruitment will be completed in July 2022.

### Protocol review and amendments

#### Sample size review

According to the original sample size estimation, 2,979 participants (993 cases and 1,986 controls) would be required to detect an odds ratio ≤ 0.70 for the primary outcome analysis, assuming the recruitment of two controls per case, a rate of complete vaccination with the Pfizer-BioNTech BNT162b2 mRNA vaccine of 60% in the control group, a two-tailed alpha of 5%, a power of 80%, and an increased sample size by 30% (due to parameter uncertainties and need for covariate adjustment). In order to achieve adequate power to assess the impact of BNT162b2 on symptomatic SARS-CoV-2 infection associated with the Gamma variant (predominant SARS-COV-2 lineage at the time of study protocol development), considering a rate of 32.5% of genotyping tests with inconclusive results and a prevalence of 90% of the Gamma variant, the original sample size was determined to be 4,500 participants (1,500 cases and 3,000 controls).

In January 2022, the study sample size was revised, given the frequent variation of COVID-19 pandemic factors that could impact sample size estimation (e.g., emergence of Omicron variant, scarcity of new COVID-19 cases due to Gamma variant, increase in vaccine coverage, and vaccine effectiveness variations for distinct SARS-CoV-2 variants). Revision was made based solely on the number of recruited patients, number of cases and proportion of positive cases in the whole sample, without any additional analysis. The original study sample size (4,500 participants) was judged to provide an appropriate power to assess the primary outcome analysis as described in the sample size section.

#### Change in exposure definitions

Given the third vaccine dose of BNT162b2 e became part of standard of care in COVID-19 vaccination in Brazil after study approval, the primary exposure definition was changed from receipt of two doses of BNT162b2 (with the receipt of the second dose 7 days or more before the onset of symptoms of COVID-19-like illness) to receipt of two or more doses of BNT162b2 (with the receipt of the second dose 7 days or more before the onset of symptoms of COVID-19-like illness). We also added the receipt of three doses of Pfizer-BioNTech BNT162b2 mRNA vaccine (with the receipt of the third dose 7 days or more before the onset of symptoms of COVID-19-like illness) as a secondary exposure variable. No data was analysed for this protocol amendment.

## Discussion

The present study has been designed as the first real-world mass vaccination city-wide study with the Pfizer-BioNTech BNT162b2 COVID-19 vaccine in Brazil. Results of this study will allow healthcare professionals, researchers, and policy makers to better understand the real-world effectiveness of BNT162b2 against prevalent variants of concern like Delta and Omicron. In addition, the present study will explore the vaccine effectiveness on relevant, but less explored, outcomes such as persistence of COVID-19 symptoms (i.e., “long COVID-19”) and occurrence symptomatic SARS-CoV-2 re-infections.

The test-negative design was chosen due to its feasibility and reliability of findings in a real-world mass vaccination context. Test-negative design studies have been extensively used to estimate vaccine effectiveness against symptomatic respiratory infections [23], including COVID-19 [24–26], while controlling for potential biases such as healthcare seeking behaviour and misclassification of COVID-19 status. Strengths of our study include the prospective ascertainment of infection status to guarantee the inclusion of case and controls with similar disease manifestation—preventing sample bias; the use of adjudication procedures to avoid recall bias of exposure factors (i.e., vaccination status); the genotyping procedures of all COVID-19 cases—allowing the assessment of vaccine effectiveness against specific SARS-CoV-2 variants of concern; and the prospective follow-up of cases to allow the evaluation of vaccine impact on COVID-19-related complications.

Our study has some limitations. First the present study design is susceptible to confounding due to differences between vaccinated and unvaccinated persons that may influence the occurrence of COVID-19. In order to minimize this potential bias, relevant risk factors for COVID-19 (both person- and time-related variables) will be used for covariate adjustment in the primary analyses. Moreover, sensitivity analyses will be conducted to assess consistency of results. Second, the sample size calculation may be inaccurate, given premises used to calculate the number of participants are highly variable based on the prevalence of COVID-19 in the study period. Third, misclassifications of cases and controls are possible, given the accuracy of RT-PCR for COVID-19 is not perfect. Nevertheless, the study protocol includes actions aimed to optimize diagnosis accuracy (e.g., exclusion of individuals at increased risk for false negative tests, use of validated RT-PCR test procedures with high sensitivity and specificity, and sensitivity analyses to assess consistency of findings under distinct test accuracy scenarios). Fourth, modifications in the standard of care regarding COVID-19 vaccination demanded changes in the definition of exposure variables to reflect the real-world practices while keeping the study procedures feasible.

Evidence regarding effectiveness of BNT162b2 in Brazil and in the southern hemisphere is limited and this study will help fill this important epidemiological gap. These data can broaden the evidence-base from clinical trials help guide effective COVID-19 vaccination policies.

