### Participants

The present study population is composed of consecutive individuals aged 12 years or older who seek the public healthcare system of Toledo with symptoms suggestive of COVID-19.

Inclusion criteria are (1) age ≥ 12 years old; (2) to be a resident of Toledo; (3) seeking care in the public healthcare system of Toledo with symptoms suggestive of COVID-19 defined as follows: acute respiratory infection symptoms (nasal congestion, rhinorrhea, anosmia, sore throat, hoarseness, new or increased-from-baseline cough, sputum production, dyspnea, wheezing, myalgia) OR admitting diagnosis suggestive of acute respiratory infection symptoms (pneumonia, upper respiratory infection, bronchitis, influenza, cough, asthma, viral respiratory illness, respiratory distress, respiratory failure), and (4) having a nasopharyngeal (NP) or nasal sample for SARS-CoV-2 diagnosis obtained as standard of care.

Patients with history of remdesivir treatment in the past 30 days, convalescent plasma treatment in the past 90 days, treatment with monoclonal antibodies for COVID-19 in the past 90 days (e.g., sotrovimab, casirivimab-imdevimab, bamlanivimab, etesivumab), and those who refused to provide informed consent are excluded. Participants are allowed to re-screen; however, the follow-up is performed considering only the first enrollment of each individual for the study.

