### Sample size

The sample size was calculated based on formulas published by O’Neill RT [9]. Assuming the recruitment of two controls per case, a vaccine coverage rate of 90% among controls, a sample of 622 cases and 1,244 controls will be required to detect a vaccine effectiveness of 80% with a precision width of 10%. Considering that around 50% of enrolled participants will fulfil criteria for the primary analysis (≥ 2 doses of BNT162b2 or unvaccinated) and increasing the sample size by 20% (due to parameter uncertainties, potential COVID-19 misclassifications, and need for covariate adjustment), the study will need to include 1,500 cases and 3,000 controls.

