#### RT-PCR procedures

Total RNA is extracted from the specimens using a viral RNA and DNA kit (MVXA-P096FAST) in an automatic nucleic acid extractor (Extracta 32, Loccus Biotecnologia, Brazil), using magnetic beads. The specimens are then tested to confirm the presence of SARS-CoV-2 genetic material using the BIOMOL OneStep/COVID-19 KIT (IBMP, Curitiba, Brazil) or using the Centers for Disease Control and Prevention 2019-Novel Coronavirus (2019-nCoV) Real-Time RT-PCR Diagnostic Panel (https://www.fda.gov/media/134922/download). This approach has demonstrated high specificity (100%) and sensitivity (88% to 98%) for COVID-19 diagnosis [12, 13].

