#### Sensitivity analyses for the primary outcome

The following sensitivity analyses will be conducted to assess consistency and risk of bias: (1) performing multiple imputation for missing core variables data (see *handling missing data section*); (2) considering only the first enrollment of each individual for the study; (3) excluding as controls those with less than 5 days of symptom onset.

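### The limitations section claims that people at increased risk of a false-negative test are excluded, but no rule limits the time from symptom onset to swab, so late-swabbed COVID-19 patients who test negative can count as controls

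*Protocol article*

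**What the plan says.** The Discussion accepts that RT-PCR can misclassify cases and controls, and lists safeguards that the protocol is said to include. The first two are "exclusion of individuals at increased risk for false negative tests, use of validated RT-PCR test procedures with high sensitivity and specificity".

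The Participants section gives the eligibility rules. On symptoms, a person must be "seeking care in the public healthcare system of Toledo with symptoms suggestive of COVID-19 defined as follows: acute respiratory infection symptoms" (a list follows), or have an admitting diagnosis of that kind. On the sample, the rule is "having a nasopharyngeal (NP) or nasal sample for SARS-CoV-2 diagnosis obtained as standard of care". The exclusions begin "Patients with history of remdesivir treatment in the past 30 days, convalescent plasma treatment in the past 90 days", continue with monoclonal antibodies in the past 90 days, and end with refusal of consent. No number of days from onset to swab appears.

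The Primary outcome analysis section adds no such limit. Time since onset is used to select participants only once, in sensitivity analysis (3): "excluding as controls those with less than 5 days of symptom onset".

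The RT-PCR procedures section credits the assay with "high specificity (100%) and sensitivity (88% to 98%) for COVID-19 diagnosis".

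**The concern.** In a test-negative design, a missed case does not drop out; it becomes a control. Missed cases carry the vaccination coverage of cases, which is lower than that of true non-cases if the vaccine works. Mixing them into the controls lowers control coverage and moves the odds ratio toward 1.

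A limit on the time from onset to swab is a usual guard against this. The Discussion reads as if some guard of this kind were in place. The criteria show none for late sampling, and sensitivity analysis (3) acts on the other end of the time scale: with early-swabbed controls removed, late-swabbed ones form a larger share of those that remain. A reader who relies on the Discussion would credit the primary estimate with a protection that the stated rules do not give. A larger sample does not reduce this kind of bias.

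**Working it through.** **Inputs from the article.** The Sample size section assumes "Assuming the recruitment of two controls per case, a vaccine coverage rate of 90% among controls", a VE of 80% and a precision width of 10%. Sensitivity is 88% to 98% and specificity 100% (RT-PCR procedures). The interval is 95% Wald and VE = 1 − OR (Primary outcome analysis).

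**Step 1: reproduce the planned precision.**
- Control odds of vaccination: 0.90/0.10 = 9.
- Case odds: 0.20 × 9 = 1.8, so case coverage is 1.8/2.8 = 64.3%.
- SE(ln OR) at 622 cases and 1,244 controls: √[1/(622 × 0.643 × 0.357) + 1/(1,244 × 0.90 × 0.10)] = √(0.00700 + 0.00893) = 0.1262.
- Interval for OR: 0.20 × exp(±1.96 × 0.1262) = 0.156 to 0.256, so VE is 74.4% to 84.4%, a width of 10.0 points.

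The stated 622 cases reproduce exactly. The planned half-width is about 5 points.

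**Step 2: false negatives among controls, equal sensitivity *s* in vaccinated and unvaccinated cases.** Each detected case implies (1 − s)/s missed ones. With two observed controls per detected case, the share of controls that are missed cases is f = (1 − s)/(2s). Control coverage becomes 0.90 − f × (0.900 − 0.643). Coverage among detected cases is unchanged.

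| s | f | control coverage | control odds | observed VE = 1 − 1.8/odds |
|---|---|---|---|---|
| 98% | 1.0% | 89.7% | 8.74 | 79.4% |
| 88% | 6.8% | 88.2% | 7.51 | 76.0% |

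The loss is 0.6 to 4.0 points, and it covers false negatives from every cause.

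At an assumed true VE of 50%, case odds are 4.5 and case coverage is 81.8%. The same steps give control odds of 8.92 and 8.47, and VE of 1 − 4.5/8.92 = 49.5% and 1 − 4.5/8.47 = 46.9%.

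**Step 3: sensitivity that differs by vaccination status.** The two ends of the article's range are assigned to the two groups (the assignment is an assumption).
- 88% in vaccinated and 98% in unvaccinated cases: observed VE 82.2%.
- 98% in vaccinated and 88% in unvaccinated cases: observed VE 72.7%.

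The bias can therefore go up or down.

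**Step 4: what a window and sensitivity analysis (3) would do.** This is an illustration on assumed figures, because the article gives no distribution of onset-to-swab time. Assume that 20% of cases and of non-cases are swabbed late, that sensitivity is 98% early and 50%, 70% or 88% late, and that it does not depend on vaccination. Overall sensitivity is then 88.4%, 92.4% or 96.0%, inside the article's range. For simplicity, sensitivity analysis (3) is taken to leave only the late group among controls, with all cases kept.

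| late sensitivity | no window | late swabs excluded | sensitivity analysis (3) |
|---|---|---|---|
| 50% | 76.2% | 79.3% | 65.8% |
| 70% | 77.6% | 79.4% | 71.4% |
| 88% | 78.8% | 79.4% | 76.5% |

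Under these assumptions a window recovers most of the loss, and sensitivity analysis (3) moves further from the true 80%.

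**The case against.** Several objections have force.

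- **The Discussion never mentions late swabs.** The exclusions for remdesivir, plasma and antibodies may be what its authors had in mind. A reader might infer that the claimed safeguard is simply absent; the article does not support that. What stands is narrower: those exclusions do nothing for an untreated person swabbed late.
- **Eligibility asks for acute symptoms, and for cough that is new or worse than baseline.** A reader might infer that someone three or four weeks into an illness plainly qualifies. The word *acute* makes that doubtful. It is still not a number of days, and it does not work as a sampling window.
- **The size is easily overstated.** If 10% of controls were missed cases, VE would fall to 74.1%, a loss of about 6 points. But f = 0.10 with two controls per case implies s = 1/1.2 = 83%, below the article's 88%. The article's figures support a loss of at most 4.0 points from all false negatives.
- **The direction is conditional.** A pull toward zero cannot be asserted outright, as Step 3 shows.
- **The article gives no time course for RT-PCR positivity.** That late samples are more often negative is therefore an assumption here, as is any particular cutoff.
- **Misclassification is acknowledged.** The sample is inflated by 20% partly on this account, and the Discussion mentions sensitivity analyses under different test-accuracy scenarios. Inflation does not remove bias, however, and the three listed sensitivity analyses contain no such scenario unless item (3) is meant.
- **The article condenses a fuller protocol, and local testing policy is not shown.** A limit may exist in practice. The mismatch between the article's own sections remains.

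**Conclusion.** The point holds in a limited form. The Discussion claims an exclusion that the printed criteria do not provide for late sampling, the primary analysis sets no onset-to-swab limit, and the only timing rule works at the other end. The three sections need to be reconciled.

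With the planning values of 90% control coverage, two controls per case and a true VE of 80%, and with sensitivity unrelated to vaccination, false negatives from all causes cost 0.6 to 4.0 points against a planned half-width of about 5. How much of that is due to late swabs cannot be said from the article. Without the equal-sensitivity assumption, even the sign is open. This is a cheap improvement to the plan, not a demonstrated material bias in the primary result.

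**What to change.** Restrict the primary analysis set, for cases and controls alike, to swabs taken within a prespecified number of days from symptom onset, and report the unrestricted set as a sensitivity analysis. Ten days would serve as an example; the article offers no basis for a particular figure, so the sponsor should fix and justify one before the data are analysed.

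No new data are needed. The exposure definitions already require the onset date, and the reference group and calendar-time covariate already require the sample date. The cost is the loss of late-swabbed participants from the primary set, a share that the article does not give, and a somewhat narrower analysed population.

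If no window is adopted, correct the Discussion so that it names the exclusions that the Participants section actually contains.
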